## Abstract

**Background:**

Levels of self-perceived psychological resilience are low to moderate among youth with chronic musculoskeletal pain (CMP). Furthermore, resilience has been associated with symptom severity in CMP. Resilience coaching programs may therefore be of benefit in the nonpharmacologic management of adolescent CMP and may serve as an adjunctive way to access mental health services in an approachable and affordable way.

**Objective:**

The main goal of the study is to assess the feasibility, acceptability, and preliminary efficacy of the resilience coaching program called Promoting Resilience in Stress Management (PRISM) and to obtain the data needed to plan a larger trial.

**Methods:**

The Resilience Coaching for Adolescents with Chronic Musculoskeletal Pain pilot study is an investigator initiated, 2-arm, randomized controlled trial (RCT) of PRISM in the interdisciplinary management of CMP among adolescents. The study will compare usual care versus PRISM+usual care among adolescents newly diagnosed with CMP in the outpatient setting. One caregiver per patient will also be enrolled. The control group will receive usual care with no specific intervention. The treatment arm will receive PRISM, which is a remotely delivered, 1-on-1resilience coaching program, consisting of 4 required skill-based sessions and an optional final session. Sessions will be delivered every 1-2 weeks, lasting about 3 months in total. The primary outcome is the Functional Disability Inventory (FDI) score at 3 months postrandomization. The secondary objectives are to evaluate potential patient- and caregiver-level moderators of PRISM and identify facilitators of and barriers to engagement in PRISM. The estimated sample size is 65 patient-caregiver dyads per group, for a total of 130 dyads.

**Results:**

The trial is currently open. Initial Institutional Review Board approval was obtained on April 4, 2023, and protocol version 4 was amended on January 14, 2025. Recruitment began on May 8, 2023, and recruitment is anticipated to be completed on August 1, 2025.

**Conclusions:**

Resilience coaching has demonstrated excellent feasibility, acceptability, and efficacy in teenagers with chronic illness; however, evidence to support its use in adolescent CMP is lacking. Resilience coaching has the potential to improve patient outcomes in this population. This pilot RCT will demonstrate acceptability, feasibility, and preliminary efficacy and reveal critical barriers to and facilitators of engagement. This will inform a larger multisite trial to evaluate the definitive efficacy of the intervention.

**Trial Registration:**

ClinicalTrials.gov NCT05834725; https://clinicaltrials.gov/study/NCT05834725.

**International Registered Report Identifier (IRRID):**

DERR1-10.2196/73385

## Introduction

Chronic musculoskeletal pain (CMP), or pain in the bones, joints, and tissues lasting longer than 3 months [1], is a common condition affecting up to 25% of children and adolescents [2]. Many adolescents with CMP experience significant psychological distress [3], exhibiting higher levels of depression and anxiety than youth without CMP [4]. Further elucidating the relationship between stress and pain, higher pain intensity in adolescents with CMP is associated with greater emotional and behavioral challenges [5]. Along with these mental health challenges, CMP is also associated with functional disability in various domains, including school attendance, reduced social contact, sleep problems, and family functioning [6].

The current standard of care treatment for adolescent CMP consists of nonpharmacological, interdisciplinary care combining physical, occupational, and psychological therapies [7-10]. These treatments require intensive physical activity, which can be both physically and emotionally taxing. Mental health interventions are a key element of this multimodal treatment approach, with cognitive behavioral therapy (CBT) being the most common [10]. However, many patients encounter months-long waitlists to access specialized interdisciplinary pain care.[11]

Considering that experiencing chronic pain and adhering to CMP treatment recommendations can be significant life stressors, researchers have proposed psychological resilience as a method of coping with chronic pain [12,13]. Adolescents with CMP have been demonstrated to have low-to-moderate self-perceived psychological resilience [14], which is defined as “a dynamic process of positive adaptation or continued development in the context of significant adversity” [15,16]. Higher levels of resilience in youth with CMP have been found to correlate with lower symptom severity, increased function [14], and reduced odds of suicidality [17]. Thus, further research is needed to establish whether interventions targeted at increasing resilience can improve pain coping, ultimately leading to improvements in pain-related clinical outcomes, such as functional disability and psychological distress. Brief resilience coaching programs also have the potential to alleviate difficulties in accessing specialized pain care, as coaching can be readily initiated in the time between initial diagnosis and a patient’s first specialized pain clinic appointment.

Promoting Resilience in Stress Management (PRISM) is a 1-on-1 resilience coaching program consisting of 5 skill-based sessions offered in person or remotely via videoconferencing or telephone for adolescents with chronic illness. PRISM’s efficacy has been shown via improved resilience, health-related quality of life, and mental health outcomes for adolescents and young adults with serious illnesses, including cancer, type I diabetes, and cystic fibrosis [18-21]. Although CBT and other evidence-based psychological strategies have strong evidence supporting their use in the treatment of pediatric chronic pain [22], the use of a resilience framework and resilience coaching has not been formally examined among youth with CMP.

Our prior single-arm pilot study to assess PRISM’s feasibility and acceptability among youth with CMP was the first effort to investigate resilience coaching in this patient population. In this study, participants completed patient-reported outcome measures (PROMs), pre- and postintervention, and both patients and caregivers provided qualitative feedback. The feedback was highly positive, reinforcing our hypothesis that PRISM offers an acceptable alternative psychosocial intervention for youth who either struggle to access mental health services or face stigma associated with them. The study also confirmed that PRISM is feasible and acceptable among youth with CMP, while exploratory analyses suggested improvements in resilience, functional disability, and psychological distress [23]. Significant changes were not observed in pain intensity, pain catastrophizing, and global health; however, we did not have a control group for comparison, nor were we powered to examine efficacy. Based on the findings of this pilot study, we determined that PRISM holds promise for the treatment of adolescent CMP and that additional work is needed to evaluate the efficacy of PRISM compared to usual care and explore factors informing its implementation.

One challenge observed during the single-arm pilot study was that 55% of participants were already engaging in psychological treatment, limiting our ability to attribute changes in PROMs solely to the effects of PRISM. Qualitative interview findings also suggested that the intervention could be of more value to those who were naive to psychological counseling. We determined that future research is needed to separate the effects of PRISM from those of CBT by excluding patients who are actively receiving CBT at the time of screening. We also intended to limit future studies to patients with mild or greater impairment due to pain in order to direct the intervention toward adolescents most in need, while increasing the possibility of demonstrating an improvement in functional disability scores. Lastly, to further assess the durability of PRISM, we planned to extend data collection beyond 3 months to include a 9-month follow-up survey. We also aimed to incorporate participant feedback from our single-arm pilot trial regarding overall helpfulness and benefits, reasons for deciding to participate, session logistics, accessibility, mental health perceptions, and caregiver interest in resilience into future protocols to better meet the needs of patients.

In this paper, we present the protocol for an ongoing pilot phase 2 randomized controlled trial (RCT) of PRISM for adolescents with CMP. The goal of this study is to determine whether the addition of PRISM to usual care demonstrates greater improvements in functional disability than usual care alone. Usual care was chosen as the comparator group to best mimic the clinical real-world setting and because denial of these services would not be ethically sound. Secondary aims include (1) determining the impact of PRISM on pain intensity and psychological distress, (2) exploring moderators of intervention effects, and (3) examining implementation outcomes of, facilitators of, and barriers to intervention engagement. This work provides the basis for a future definitive multicenter RCT to evaluate the efficacy of the intervention and feasibility of delivering resilience coaching across sites, as this will facilitate and support implementation of resilience coaching within usual care for CMP.

## Methods

### Study Design and Setting

The study was registered at ClinicalTrials.gov (NCT05834725) on April 28, 2023. This study is a single-center pilot, 2-arm, RCT using a mixed methods approach (quantitative patient outcome measures combined with qualitative interview data). Participants are recruited from an outpatient pediatric rheumatology clinic and an interdisciplinary pain clinic at the Children’s Hospital of Philadelphia (CHOP) in Philadelphia, PA, USA. See Multimedia Appendix 1 for the SPIRIT (Standard Protocol Items: Recommendations for Interventional Trials) checklist.

### The PRISM Intervention

PRISM consists of 4 required skill-based sessions that focus on stress management, goal setting, cognitive restructuring, and benefit finding (see Figure 1). The optional fifth “coming together” session focuses on discussing with a family member, with the participant’s permission, the skills that the participant found beneficial, the ones they did not, and how they can continue to implement the skills learned in the future once the program finishes. Each session is around 30-50 minutes, with sessions scheduled 1-2 weeks apart. Participants are given access to “cheat sheets” and worksheets for each session and a mobile app that can be used to practice the skills learned.

**Figure 1 figure1:**
[figure not shown]
Overview of sessions in the PRISM program. PRISM: Promoting Resilience in Stress Management.

PRISM coaches have a bachelor’s degree (at minimum), have gone through an 8-hour training and certification process for the administration of PRISM, and have practiced delivering the intervention with 2 peers to demonstrate competency. A standardized manual is used to guide PRISM coaches through each session and includes guided discussion prompts to facilitate rapport building and patient participation. Sessions are audio-recorded, and fidelity checks are conducted regularly by a supervisor. There is a standardized fidelity checklist used for scoring purposes and a safety plan to address psychological distress, as needed.

### Participants

This study includes males and females aged ≥12 and <17 years who have a new diagnosis of CMP and are coming in person for a clinic visit, and one of their parents or legal guardians. Exclusion criteria include patients (1) with isolated and localized head pain or abdominal pain, (2) with a diagnosis of complex regional pain syndrome (CRPS), (3) currently receiving CBT, and (4) not capable of understanding the study or providing assent/consent.

### Recruitment and Randomization

Eligible participants are identified by study personnel through screening of the pediatric rheumatology and subspecialty pain clinic schedule via electronic medical records (EMRs). An EMR review is conducted to confirm eligibility, and if further information is needed, an in-person or telephone query is conducted to ensure eligibility. Study personnel approach the eligible patient and a parent or legal guardian at the time of their clinic visit or retroactively via telephone. The study is introduced using the Institutional Review Board (IRB)-approved informed consent form as guidance, and all questions are answered in accordance with IRB regulations. If the patient and their parent express interest but need more time to think about it, they fill out a contact information sheet, are provided with a consent form to take home, and are contacted after the clinic visit via telephone. If eligible and interested, they can provide electronic consent (e-consent) at the time of the clinic visit (Figure 2).

**Figure 2 figure2:**
[figure not shown]
PRISM RCT recruitment, screening, and consent process. CHOP: Children’s Hospital of Philadelphia; CMP: chronic musculoskeletal pain; e-consent: electronic consent; EMR: electronic medical record; PRISM: Promoting Resilience in Stress Management; PROMIS: Patient-Reported Outcomes Measurement Information System; RCT: randomized controlled trial.

Those who are not approached at their clinic visit can be contacted retroactively via telephone and, if interested and eligible, can be e-consented via REDCap (Research Electronic Data Capture), a secure, web-based software platform designed to support data capture for research studies [24,25]. For anyone who declines participation, their reasoning is recorded in the study’s master log. Study personnel attempt to contact patient-caregiver dyads a maximum of 3 times before discontinuing recruitment efforts. Once baseline surveys are complete, the dyads will be randomly assigned to a study arm using a 1:1 allocation ratio: PRISM+usual care versus usual care.

Stratified randomization will be implemented by the study statistician in REDCap to ensure a balance in sex (male vs female) and clinic (rheumatology clinic vs interdisciplinary pain [amplified musculoskeletal pain] clinic) between the 2 study arms. The final randomization scheme will be prepared by a statistician independent of the study team to prevent bias. Study staff will not get access to randomization algorithms. Tracking of dyads and randomization will be recorded in the study’s master log.

### Medical Record Review and Questionnaires

Each enrolled participant’s medical chart will be reviewed by a study team member for information relevant to the study, including demographics, previous diagnoses, family medical history, previous surgeries, pain-related symptoms, and past treatment. Both members of each dyad will complete questionnaires at 0 months/time of enrollment; 3 months postenrollment or, if in the treatment group, immediately after intervention completion; and 9 months postenrollment. Questionnaires will be completed using an online REDCap survey. Participants will get 45 days to complete each set of questionnaires. Reminder emails or text messages (depending on participant preference) will be sent once a week to ensure completion, and reminder calls will be made a maximum of 3 times. Participants will be compensated for their time and completion of surveys. Caregivers will be paid US $20 for completion of survey 1, US $40 for completion of survey 2, and US $20 for completion of survey 3. Patient participants will be paid US $25 for completion of survey 1, US $50 for completion of survey 2, and US $25 for completion of survey 3. Should subjects request early termination, we will enumerate the next study survey as the final study survey and compensate participants with US $10 for completion of the final surveys. Next, we describe the study measures included in the questionnaires.

The patient measures are as follows:

Demographics and medical history survey. For the first set of surveys, adolescent participants will be asked whether they have or are currently receiving counseling services and physical therapy, as well as about their exercise routine and whether they perform desensitization exercises.The 10-item Connor-Davidson Resilience Scale (CD-RISC-10) [26] measures the overall sense of resilience, or ability to cope with stressors/challenges, and assesses treatment response. Higher scores (0-40) indicate greater resilience. The CD-RISC-10 has good internal consistency and test-retest reliability.The Benefit Finding Scale for Children (BFSC) [27] is a 10-item measure of benefit finding designed for children. It is a unidimensional measure and has excellent internal consistency reliability. In a sample of children with cancer, small but significant correlations were found with measures of optimism and self-esteem and a negative correlation with trait anxiety [27].The Pain Catastrophizing Scale, Child report (PCS-C) [28] is a validated self-report measure used to assess negative thinking associated with pain. Higher scores reflect higher levels of catastrophic thinking [29].The Children’s Hope Scale [30] measures hopeful thought patterns, or the perception that one’s goals can be achieved. Higher scores indicate greater hopeful thought patterns.The Children and Adolescent Mindfulness Measure (CAMM) [31-33] is a unidimensional measure of mindfulness. Higher scores indicate higher levels of mindfulness. CAMM has good psychometric properties overall.The 8-item Chronic Pain Acceptance Questionnaire Adolescent Short Form (CPAQ-A8) [34] measures pain acceptance using 4 items for each established factor (pain willingness and activity engagement) and is sensitive to treatment. It is correlated with clinically important variables, as its full-length version. Items are scored on a 5-point Likert scale (0=never true to 4=always true). Higher scores indicate more positive perceptions of pain.The Pain Self-Efficacy Scale Child (PSES-C) [35] is a 7-item measure assessing child self-efficacy for functioning normally when in pain. Items are scored on a 5-point Likert scale, with lower scores indicating higher self-efficacy. Initial validation has provided support for the PSES-C’s validity and reliability.The PROMIS (Patient-Reported Outcomes Measurement Information System) Pediatric Global Health 7 (PGH-7) [36,37] is a brief and reliable 7-item summary assessment of a child’s self-reported health. It represents an individual’s overall assessment of their health, focusing on physical, mental, and social health components. The PGH-7 is well understood by children as young as 8 years of age. The measure has test-retest reliability estimates above 0.80, indicating excellent stability. The measure is unidimensional and factor invariant by the age of the child. Raw scores are converted to T-score (SD) values. The mean score is 50 (SD 10).The Functional Disability Inventory (FDI) [38] is a measure of pain-related disability. It is a 15-item measure assessing the degree to which pain interferes with children’s physical functioning over a 2-week period. The FDI has demonstrated adequate psychometric properties in youth with CMP aged 8-18 years [38,39]. The FDI has high internal consistency, moderate-to-high test-retest reliability, and good predictive validity [38-40].The PROMIS Pediatric Numeric Rating Scale v1.0 – Pain Intensity [41] provides a numerical value for self-reported pain intensity experienced by the child in the past 7 days.The PROMIS Pediatric Bank v2.0 – Pain Interference Short Form 8a [41] measures self-reported consequences of pain.The 8-item Patient Health Questionnaire (PHQ-8) [42-46] is a reliable and valid measure of depression severity and a good screening measure in adolescents [43].The 7-item Generalized Anxiety Disorder scale (GAD-7) [47,48] has been demonstrated to be a useful screening measure for anxiety severity in adolescents (11-17 years).The Kessler-6 Psychological Distress Scale (K6) [49,50] is a 6-item scale that measures the level of psychological distress experienced in the past month. It was developed for the US National Health Interview Survey and is currently being used in Canada, Australia, and the rest of the world as part of the World Health Organization’s (WHO) world mental health initiative. The instrument strongly discriminates between community cases and noncases of *Diagnostic and Statistical Manual of Mental Disorders* (DSM)-IV psychiatric disorders, such as serious emotional distress or serious mental illness (area under the curve [AUC]=0.74-0.88) [51]. The K6 has been extensively cross-validated, including among adolescents and parents. Responses are scored on a 5-point Likert scale (total score ranging from 0 to 24). Previous studies have shown that scores≥7 are consistent with high distress, and scores≥13 meet the criteria for serious or debilitating psychological distress [49].The Pain and Symptom Assessment Tool (PSAT) [52] is a modified version of the 2010 American College of Rheumatology (ACR) criteria for fibromyalgia (FM) syndrome, which has demonstrated good specificity and sensitivity for the diagnosis of juvenile FM in adolescents [53]. The PSAT consists of 2 components: the Widespread Pain Index (WPI) and the Symptom Severity (SS) checklist. The WPI is a questionnaire that identifies pain in the past week in 19 body locations (score 0-19). The SS checklist comprises 2 components that identify the severity of cardinal symptoms on a scale from 0 (no problem) to 3 (severe problem) and the presence or absence of associated somatic symptoms. A score is assigned based on the overall number of symptoms (0-3: 0=none to 3=a great deal of symptoms). A final SS score is calculated by adding the cardinal symptoms’ scores to the somatic symptoms’ checklist scores (maximum score=12). According to the adult ACR FM criteria, a score of ≥5 and a WPI of ≥7 or an SS score of ≥9 and a WPI of 3-6 indicates a positive diagnosis for juvenile FM.The Acceptability of Intervention Measure (AIM), the Intervention Appropriateness Measure (IAM), and the Feasibility of Intervention Measure (FIM) [54,55] are 4-item measures of implementation outcomes that are often considered leading indicators of implementation success. With readability at the fifth-grade level, these measures can be administered to a wide range of stakeholders to determine the extent to which they believe an intervention or an implementation strategy is acceptable, appropriate, and feasible. The IAM items can be modified to specify a referent organization, situation, or population. Cutoff scores for interpretation are not yet available; however, higher scores indicate greater acceptability, appropriateness, and feasibility. The AIM, IAM, and FIM have demonstrated strong psychometric properties. Specifically, the measures have demonstrated content validity, discriminant content validity, reliability, structural validity, structural invariance, known-groups validity, and responsiveness to change. The predictive validity of the measures is currently being evaluated.Satisfaction with PRISM. Session-specific and overall intervention satisfaction will be measured via a 5-point Likert scale (1=very dissatisfied to 5=very satisfied). The intervention will be defined as acceptable if the mean level of satisfaction (including session-specific and overall intervention satisfaction) is ≥3.

The caregiver measures are as follows:

CD-RISC-10K6The Pain Catastrophizing Scale – Parent report (PCS-P) [56] measures parental catastrophizing about their adolescent child’s pain. The PCS-P includes 13 items concerning different catastrophic thoughts and feelings parents may have when their child experiences pain. The items are scored using a 5-point Likert-scale (0=not at all to 4=extremely). The PCS-P yields 3 subscale scores for rumination, magnification, and helplessness, as well as a total score ranging from 0 to 52.The Adult Hope Scale (AHS) [57] measures Snyder’s cognitive model of hope, which defines hope as a “positive motivational state that is based on an interactivity derived sense of a) agency (goal-directed energy), and b) pathways (planning to meet goals).” The AHS consists of 12 items. Four items measure pathways thinking, four items measure agency thinking, and four items are fillers. Participants respond to each item using an 8-point scale ranging from definitely true to definitely false. When administering the scale, it is called the Future Scale. The agency subscale score is derived by summing items 2, 9, 10, and 12. The pathways subscale score is derived by adding items 1, 4, 6, and 8. The total AHS score is derived by summing the 4 agency and the 4 pathway items.The PROMIS Global Health (GH-10) measure version 1.2 [58] is a brief and reliable 10-item summary of an adult’s self-reported physical and mental health. It was developed as part of the US National Institutes of Health’s (NIH) PROMIS initiative using item response theory and rigorously validated in a sample of >20,000 people, primarily from the community. It is freely available and can be used across diseases with T-scores normalized to the US general population. It takes adults no more than 1-2 minutes to complete. Raw scores are converted to T-score (SD) values. The mean score is 50 (SD 10). Higher T-scores reflect more of the trait being measured.

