### Treatment Group

Patients randomized to the treatment (PRISM+usual care) group will complete the first PRISM session within ~45 days of enrollment. Patients will complete the PRISM sessions remotely using a HIPAA (Health Insurance Portability and Accountability Act)-complaint videoconferencing platform. Each session will be scheduled approximately 1-2 weeks apart but must be completed within 45 days of the previous session. We will invite each patient-parent dyad to participate in an optional 30-minute semistructured interview (see Multimedia Appendix 2 for the interview guide) that will ask about their thoughts regarding PRISM, including background, timing, duration, attendance, content, sessions, and overall satisfaction. Participants will be purposively selected to enrich the cohort for those with early dropout and ensure representation of a variety of ages, races, and ethnicities. These interviews will be conducted by a study staff member other than the PRISM coach, and they will be audio-recorded and transcribed verbatim for qualitative assessment. Participants will be paid US $25 each for their time and completion of semistructured interviews.

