### Statistical Analysis

The primary objective of this study is to determine whether PRISM, along with usual care, reduces functional disability more than usual care alone. The primary outcome or measure of efficacy is the FDI score at 3 months postrandomization (control group) or postintervention. The secondary efficacy outcomes are patient psychological distress (as measured with the K6), as well as the patient-reported pain intensity (as measured with the PROMIS Pediatric Numeric Rating Scale v1.0 – Pain Intensity). The secondary objectives are to determine a reduction in pain intensity and psychological distress with PRISM at intervention completion; determine reductions in functional disability, pain intensity, and psychological distress with PRISM at 6 months postintervention; evaluate potential patient- and caregiver-level moderators of PRISM; examine implementation outcomes (feasibility, acceptability, appropriateness); and identify facilitators of and barriers to engagement in PRISM.

The study team plans to publish the study findings in a peer-reviewed pediatrics, psychology, or rheumatology journal to disseminate the findings. No individually identifiable protected health information will be published. Summary results will be available on ClinicalTrials.gov.

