#### Quantitative Data

Quantitative measures will be used to assess the primary and secondary efficacy outcomes, moderators of PRISM, and implementation outcomes. Demographics and baseline clinical characteristics will be summarized by standard descriptive summaries (eg, means and SDs for continuous variables, such as age, and percentages for categorical variables, such as gender). The primary analysis will use an intention-to-treat (ITT) approach to mitigate confounding from nonrandom participant attrition. We anticipate a total of 100 evaluable subjects. To ensure valid randomization, we will assess demographic and clinical features, along with baseline measures of outcomes, such as physical function, pain intensity, and psychological distress, and compare the intervention to the control arm. The primary outcome will be functional disability (FDI score) assessed at the end of the intervention (month 3). The key predictor is PRISM. Secondary outcomes will include the FDI score at the conclusion of the observation period (month 9, 6 months postintervention) and psychological distress (K6 total) and pain intensity (PROMIS Pediatric Numeric Rating Scale v1.0 – Pain Intensity) at both 3 and 9 months.

Assuming balanced arms postrandomization, we will evaluate the differences in clinical outcomes between the 2 arms at months 3 and 9 using 2-sample Student *t* tests. Longitudinal changes from month 3 to month 9 will be assessed using MANOVA (multivariate analysis of variance) and linear mixed effects models to account for within-subject correlation due to repeated measures. The linear mixed effects model can additionally adjust for a few known prognostic covariates, such as fulfillment of criteria for juvenile FM. Similar analyses will examine outcomes of psychological distress and pain intensity separately.

Linear regression will be conducted to assess the association between the change in FDI scores and changes in the intervention targets, adjusted for baseline covariates of interest. These analyses will be repeated to examine correlations between changes in secondary outcomes (pain intensity and psychological distress) and hypothesized intervention targets at month 3, and we will conduct multivariable linear regression models, adjusting for covariates of interest.

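### The primary FDI assessment is timed by calendar in the control arm and by programme completion in the PRISM arm, so follow-up can differ between arms in an unknown direction

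*Protocol article*

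**What the plan says.** The article describes the primary time point in four places, and they do not agree.

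- **Abstract, Methods:** "The primary outcome is the Functional Disability Inventory (FDI) score at 3 months postrandomization", with no distinction between arms.
- **Medical Record Review and Questionnaires:** after baseline, surveys are due at "3 months postenrollment or, if in the treatment group, immediately after intervention completion; and 9 months postenrollment". Each set of questionnaires stays open for 45 days in both arms.
- **Statistical Analysis:** "The primary outcome or measure of efficacy is the FDI score at 3 months postrandomization (control group) or postintervention".
- **Quantitative Data:** the outcome is "functional disability (FDI score) assessed at the end of the intervention (month 3"), so programme end and month 3 are treated as the same moment.

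On session timing, the Abstract says "Sessions will be delivered every 1-2 weeks, lasting about 3 months in total". The Treatment Group section asks for the first session within roughly 45 days of enrollment. It plans later sessions one to two weeks apart, but each only "must be completed within 45 days of the previous session". Four sessions are required and a fifth is optional, although the feasibility paragraph of Quantitative Data counts the fifth among the required ones.

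The between-arm comparison at months 3 and 9 is a two-sample Student t test, and the primary analysis follows intention to treat.

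**The concern.** A randomized comparison is protected when both arms are measured at the same time from randomization. Here one arm is measured on a calendar date and the other on an event that exists only in that arm and depends on how quickly the participant attends sessions. If FDI drifts under usual care, a difference in mean assessment time produces a difference in mean FDI that is not an effect of PRISM.

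Drift is plausible. Participants are newly diagnosed, usual care includes exercise and desensitization, and participants may begin mental health treatment during follow-up. More elapsed time can therefore also mean more co-treatment.

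A second problem concerns the analysis population. A PRISM participant who stops attending never reaches the event that triggers the survey. Such participants are foreseeable: the feasibility criterion accepts 70% session completion, and the interview sample is to be enriched for early dropout. An intention-to-treat analysis needs a primary assessment date for them.

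**Working it through.** **1. Inputs from the article.** First session 0 to 45 days after enrollment; planned gap 7 to 14 days; permitted gap up to 45 days; 4 sessions, or 5 with the optional one; survey window 45 days. Table 1: FDI SD 11.8, 100 evaluable (50 per arm under 1:1 allocation), detectable difference 5.0. A month is taken as 30.4 days, so 3 months is about day 91 and 9 months about day 274.

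**2. When the PRISM survey opens.** Day = delay to first session + (number of sessions − 1) × gap.

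| Case | Calculation | Day | Against control day 91 |
|---|---|---|---|
| 4 sessions, weekly, no delay | 0 + 3×7 | 21 | 70 days earlier |
| 4 sessions, fortnightly, latest start | 45 + 3×14 | 87 | 4 days earlier |
| 5 sessions, weekly, no delay | 0 + 4×7 | 28 | 63 days earlier |
| 5 sessions, fortnightly, latest start | 45 + 4×14 | 101 | 10 days later |
| 4 sessions, every limit used | 45 + 3×45 | 180 | 89 days later |
| 5 sessions, every limit used | 45 + 4×45 | 225 | 134 days later |

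The no-delay rows are lower bounds, since randomization must come first.

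**3. Check of the stated duration of about 3 months.** At planned spacing it is approached only at the slow end. A four-session participant on plan always finishes before day 91. A five-session participant on fortnightly spacing reaches day 91 only by starting on day 35 or later (91 − 4×14 = 35).

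**4. Adding the survey window.** Controls can answer from about day 91 to day 136. PRISM surveys can close as late as 180 + 45 = day 225, or 225 + 45 = day 270 with the fifth session. The window is equally long in both arms but starts from a different point, so it does not align them.

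**5. Effect on the comparison.** Bias = (usual-care FDI change per month) × (mean gap in months). The article gives neither factor, so both are assumed. SE of the difference = 11.8 × √(2/50) = 2.36. Rejection probability under no PRISM effect uses the normal approximation at two-sided 5%.

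| Assumed change per month | 30-day mean gap: bias | Rejection | 60-day mean gap: bias | Rejection |
|---|---|---|---|---|
| 0.5 points | 0.49 | 5.5% | 0.99 | 7.0% |
| 1 point | 0.99 | 7.0% | 1.97 | 13.3% |
| 2 points | 1.97 | 13.3% | 3.95 | 38.7% |

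The sign follows the gap. If patients improve, a later PRISM survey favours PRISM and an earlier one counts against it. The 5-point difference serves here only as a yardstick: a 1-month mean gap corresponds to about 10% to 40% of it (0.5/5 to 2/5).

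**The case against.** The best defence is that assessment at the end of treatment is a recognized choice, that the programme is meant to last about 3 months, and that this is a single-center pilot of preliminary efficacy. If sessions run so that mean completion falls near month 3, the mean bias may be small. This stands as a limit on the size of the problem. It does not remove the arm-specific rule or the conflict between sections.

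It can also be said that survey triggers for non-completers belong in the full protocol or operating manual, and that the questionnaire rule could be read as 3 months by default with programme end for those who finish. That reading is possible, but the text does not settle it, and completers would still be timed differently from controls. The early-termination provision makes the next survey the final one, but in the PRISM arm that survey has no stated date for someone who has not finished.

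Several stronger readings are tempting and are not supported:

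- **That the design favours PRISM.** Planned spacing mostly puts PRISM at or before the control date, so with improving patients the bias could run against PRISM. Days 180 and 225 require every limit to be used and are outer bounds, not typical values.
- **That controls are measured on one fixed day.** They have the 45-day window too.
- **That month 9 is also unequal.** The third survey is set at 9 months after enrollment in both arms. Calling it "FDI score at the conclusion of the observation period (month 9, 6 months postintervention") is a loose label.
- **That anchoring to enrollment rather than randomization causes bias.** Both arms are randomized after the baseline surveys, so any lag between the two is balanced by design.

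**Conclusion.** The point holds as a defect in the stated rule, not as a demonstrated bias. The article defines the primary assessment differently by arm and then treats it as a common month 3. Its own session limits let the PRISM assessment open about 70 days before the control date, or 89 days after it (134 with the fifth session). The timing depends on behaviour after randomization, and the stated t test makes no allowance for it. PRISM participants who do not finish have no clearly defined primary date, which sits badly with intention to treat.

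The size and sign of any bias cannot be obtained from the document. The figure of 0.5 to 2 points for a 1-month mean gap, in either direction, rests on an assumed usual-care change of 0.5 to 2 points per month and an assumed mean gap. A reader who infers a specific spurious benefit for PRISM goes beyond what the article supports.

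**What to change.** **Definition.** State the primary time point once, as 3 months after randomization in both arms with the same 45-day window. Send the survey whether or not PRISM sessions are finished, and align the Abstract, Medical Record Review and Questionnaires, Statistical Analysis and Quantitative Data sections with it. Session delivery need not change.

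**PRISM-only ratings.** Collect satisfaction and the AIM, IAM and FIM separately at programme end, so that they no longer dictate when the FDI is measured.

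**Surveys already completed.** Report the distribution of actual assessment times by arm. As a sensitivity analysis, fit the planned linear mixed model with actual time since randomization. This is only a partial remedy, because PRISM timing is itself a post-randomization variable. Restricting to surveys inside a common window is no cure either, since it selects PRISM participants on their session pace.

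**Month 9.** Leave the schedule as it is and drop the label that calls it six months after the intervention.

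**Cost.** A change to the REDCap survey trigger, a short amendment and a sentence in the analysis plan. Some PRISM participants will be assessed before their last session. Recruitment was due to finish on August 1, 2025, so the new trigger reaches only those not yet surveyed and leaves two timing rules in one trial. The report should say how many participants fell under each.
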